This study aims to evaluate the effectiveness and cost-effectiveness of the culturally adapted EASE intervention compared with wait-list control to improve psychosocial distress in adolescents and improve caregiver-adolescent relationship and caregivers’ well-being at 3 months postintervention in public school settings of Pakistan.

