## Methods and analysis

### Study design

A two-arm, single-blind, cRCT, with a wait-list control arm and an embedded qualitative study is being conducted in public schools of rural subdistrict of Gujar Khan in Rawalpindi, Pakistan. The unit of randomisation is a school. In this study, 40 eligible school clusters, stratified by gender, have been randomised into intervention and control arms with a 1:1 allocation ratio. Outcomes will be assessed at baseline and 1 week and 3 months postintervention.

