**Figure 1 F1:**
[figure not shown]
Flow of participants through cRCT

For the analysis of the primary outcome (reduction in PSC psychosocial distress scores from baseline to 3 months’ post intervention follow-up), a linear mixed model will be employed with treatment, visit, interaction between treatment and visit as fixed effects, gender and the baseline value of the PSC psychosocial distress score as covariates, subject and cluster (school cluster) as random effects. In addition, adjusted linear mixed model analysis will be performed with the pre-specified covariates (parent/primary caregivers’ education) measured at baseline being added into the above linear mixed model, which will be identified and listed in the statistical analysis plan. The crude and adjusted mean differences in the primary outcome together with its 95% CIs between intervention and control at 3 months will be derived from the mixed models. In addition, subgroup analysis of primary endpoint will be performed on the above pre-specified covariates. Analysis of secondary continuous outcomes with single follow-up measurement will be done using a linear mixed model with treatment as fixed effect, gender and the baseline value of the outcome variable as covariates and cluster (school cluster) as random effect. Analysis of secondary continuous outcomes with repeated follow-up measurement will be performed in a similar fashion as the primary endpoint analysis. The analysis of binary outcomes will use a generalised linear mixed model with treatment as fixed effect, baseline measurement of the outcome variable and gender as covariates, subject and cluster (school cluster) as random effects. The generalised linear mixed model will have a binomial distribution and logit link function, which will generate ORs with their 95% CIs of having an event between intervention and control.

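### The binary-outcome model has a subject random effect but no visit or treatment-by-visit term, so for an outcome measured twice its single OR averages 1 week and 3 months

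*Protocol article*

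**What the plan says.** The Statistical analysis section of the protocol article sets out three model structures.

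- **Primary outcome, and continuous secondary outcomes with repeated follow-up.** The fixed effects are "treatment, visit, interaction between treatment and visit as fixed effects", with gender and baseline as covariates and subject and school as random effects. The extension to secondary outcomes reads "Analysis of secondary continuous outcomes with repeated follow-up measurement will be performed in a similar fashion as the primary endpoint analysis".
- **Continuous secondary outcomes with one follow-up.** The model has "treatment as fixed effect, gender and the baseline value of the outcome variable as covariates and cluster (school cluster) as random effect". There is no subject effect.
- **Binary outcomes, without distinction by number of follow-ups.** The model has "treatment as fixed effect, baseline measurement of the outcome variable and gender as covariates, subject and cluster (school cluster) as random effects". It uses a binomial distribution and logit link, "which will generate ORs with their 95% CIs of having an event between intervention and control". No time point is named for the OR.

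The Study design section gives two post-baseline visits: "Outcomes will be assessed at baseline and 1 week and 3 months postintervention". The aim, at the end of the Introduction, is set "well-being at 3 months postintervention in public school settings of Pakistan".

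**The concern.** The binary model takes its random effects from the repeated-measures structure and its fixed effects from the single-follow-up structure. The plan separates one follow-up from two for continuous outcomes and drops that separation for binary ones.

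The combination fits neither case well. With two visits per pupil, a single treatment coefficient must serve both visits, and nothing lets the event rate change between them. With one binary value per pupil, there is nothing to separate a subject variance from the binomial variation.

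At stake is how a binary result would be read. The aim and the primary contrast are both at 3 months, so a reader would probably take an unlabelled OR as a 3-month effect. If the effect fades after the sessions end, the pooled OR would look more favourable than the 3-month one. If it grows, the pooled OR would dilute it.

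**Working it through.** The plan gives no figure to reproduce for binary outcomes. The visit schedule and model terms come from the protocol article. All event rates, effect sizes and subject SDs below are assumptions made for illustration.

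**1. The three specifications side by side**

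| Outcome type | Visit, treatment × visit | Subject random | School random |
|---|---|---|---|
| Continuous, repeated (and primary) | yes | yes | yes |
| Continuous, one follow-up | no | no | yes |
| Binary, any | no | yes | yes |

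The third row matches neither of the first two.

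**2. Two follow-ups: what the single OR measures**

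Odds = p/(1 − p), and OR = odds (intervention) / odds (control). Without a visit term, the treatment contrast rests on event proportions averaged over the visits. These are marginal ORs. The mixed model's conditional OR lies further from 1 but averages the visits in the same way.

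*Case A, fading effect: 60% v 40% at 1 week, 55% v 48% at 3 months.*
- 1 week: (0.60/0.40) / (0.40/0.60) = 1.500/0.667 = 2.25
- 3 months: (0.55/0.45) / (0.48/0.52) = 1.222/0.923 = 1.32
- Averaged proportions: (0.60 + 0.55)/2 = 0.575 and (0.40 + 0.48)/2 = 0.44
- Pooled: (0.575/0.425) / (0.44/0.56) = 1.353/0.786 = **1.72**, against 1.32 at 3 months

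*Case B, effect gone by 3 months: 62% v 40%, then 50% v 50%.*
- 3-month OR = 1.00
- Averaged proportions: 0.56 and 0.45
- Pooled: (0.56/0.44) / (0.45/0.55) = 1.273/0.818 = **1.56** (about 2.07 conditional on a subject SD of 2)

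*Case C, constant effect: 60% v 40% at both visits.*
- 1-week, 3-month and pooled OR are all 2.25, so there is no discrepancy

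*Simulated fit of the stated model* (40 schools of 14, school and subject normal intercepts, gender and baseline included, 12 runs). The true conditional log ORs were −1.0 at 1 week and −0.3 at 3 months, that is ORs of 0.37 and 0.74. The model returned a mean log OR of −0.64 (simulation SE 0.07), an OR of 0.53. The midpoint of the two log ORs is (−1.0 − 0.3)/2 = −0.65, so the estimate is an average over visits. The subject variance itself was well identified with two values per pupil. In one data set with a true SD of 1.5, the log-likelihood was −679.8 at SD 1.5 against −702.0 at SD near 0.

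**3. One follow-up: what determines the subject variance**

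The same simulated structure was used with one binary value per pupil, and the subject SD was fixed at successive values.

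| Subject SD | Maximised log-likelihood | Conditional OR |
|---|---|---|
| 0 (0.001) | −355.18 | 0.41 |
| 0.5 | −355.15 | 0.39 |
| 1 | −355.12 | 0.34 |
| 1.5 | −355.09 | 0.29 |
| 2 | −355.08 | 0.24 |
| 3 | −355.07 | 0.15 |

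The log-likelihood moves by 0.11 units over the whole range, while the OR falls from 0.41 to 0.15. The data barely distinguish these values, and the reported OR follows whichever SD the fit settles on.

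**The case against.** **No binary endpoint is named.** This stands. The Hypotheses, Table 1 and the outcome sections list scores, service use and cost, with no responder or caseness endpoint. The point reaches only derived or secondary analyses, for example PSC below its cut-off of 28. It still has an object, because the plan commits to binary ORs and states the terms, link and effect measure.

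**The single-follow-up case may be empty.** This also stands. In Table 1 only the self-stigmatisation scale and the service-receipt inventory have one follow-up. The first is a Likert score with no baseline. The second serves the cost analysis, and no binary version of it is defined.

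**A common OR over visits is a legitimate quantity.** It is estimable, and it equals the 3-month OR if the effect is constant (Case C). But the plan's own repeated-measures model does not assume constancy, and no reason is given for assuming it here. The 3-month target for binary outcomes is inferred from the aim and the primary contrast, since the binary sentence names no time point.

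**A vanished effect would be visible anyway.** Categorical variables are to be tabulated by arm and visit, which would help an attentive reader. It does not supply a 3-month OR with a CI.

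**The SAP will give the detail.** It may. But the article states this model explicitly, so a SAP that follows it inherits the problem, and one that departs from it contradicts the published plan.

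**Stronger readings.** A reader might infer that no binary outcome could give a valid OR, or that the likelihood is exactly flat in the subject variance. The documents do not support the first: with two visits the model is estimable and its OR has a meaning. The second holds exactly only for a bare two-arm comparison. With school and covariates in the model, the variance is very weakly identified through the shape of the link. Nor is a conditional OR an error in itself, since any logit mixed model gives one.

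**Conclusion.** The concern holds, with limited reach. The stated binary model is inconsistent with the plan's own rules for continuous outcomes. For a binary outcome measured at both visits, its OR is an average over 1 week and 3 months, and it is the 3-month effect only if the effect does not change. The illustrated gap is 1.72 against 1.32 for a fading effect, and nil for a constant one. The size depends wholly on assumed rates; the mechanism does not. For any binary outcome with one follow-up, the subject variance is practically unidentified and the conditional OR depends on it.

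A reader might take this as a defect in the trial's main result. It is not: the primary analysis includes visit and treatment-by-visit and takes its contrast at 3 months, and the continuous secondary models are also unaffected. This is a moderate to minor correction.

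**What to change.** Apply the plan's own continuous-outcome rule to binary outcomes, in the SAP and in any protocol update:

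- **Repeated follow-up:** treatment, visit and treatment × visit as fixed effects; gender and baseline as covariates; subject and school random. Report the OR with 95% CI at 3 months, and separately at 1 week.
- **Single follow-up:** treatment as fixed effect; gender and baseline as covariates; school as the only random effect.

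The SAP should also name each binary outcome to which these models apply. Standardised ORs and risk differences are an optional addition.

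The cost is wording only, with no new data. The 3-month OR will have a slightly wider CI than an OR pooled over both visits.

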**Method and analysis:**

A two-arm, single-blinded, cluster randomised controlled trial, with a wait-list control arm is being conducted in school settings of rural Pakistan. Forty eligible public-school clusters have been randomised (stratified by gender) on a 1:1 allocation ratio into intervention (n=20) and control arm (n=20). Following informed consent, 564 adolescents with psychosocial distress (Youth-reported Paediatric Symptoms Checklist, cut-off ≥28) from 40 schools have been enrolled into the trial (14±3 average cluster size) between 2 November 2021 and 30th November 2021. Participants in the intervention arm will receive EASE in 7-weekly adolescents and 3-biweekly caregivers group sessions in schools. The adolescent sessions involve the components of psychoeducation, stress management, behavioural activation, problem-solving and relapse prevention. Caregivers will receive training to learn and implement active listening; spending quality time and using praise as a strategy to help their children. The primary outcome is reduction in psychosocial distress at 3 months postintervention. Secondary outcomes include symptoms of depression and anxiety, caregiver–adolescent relationship and caregivers’ well-being. Outcomes will be assessed at baseline, immediate 1 week and 3-months postintervention. Qualitative process evaluation will explore barriers and facilitators to programme implementation in low-resource school settings.

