### Sample size calculations

The cluster unit of randomisation has been defined at the school level, stratified by gender. Based on other school-based and community-based mental health interventions using the measures assessing psychosocial problems in children,^15 16^ we assume an effect size of 0.4 at 3 months’ postintervention follow-up, with 80% power, 0.05 significance, an ICC of 0.05 and a two-sided hypothesis test with 40 school clusters randomised with a 1:1 allocation ratio, stratified by gender and accounting for 20% attrition. This results in a total of 550 adolescents (ie, 225 in each arm) and about 14 adolescents from each school. Each high school has about 150 adolescents in grade 8 and 9, which is more than sufficient to meet our sample size requirement. Stratification by gender will minimise imbalance between groups by factors likely to be associated with our outcome and reduce the between-cluster variability, hence increasing the power of the study.

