Service cost data will subsequently be linked to primary and secondary study outcomes, in particular internalising symptoms scores to assess issues around the value or cost-effectiveness of the EASE intervention. In the event that dominance is not shown, that is, the EASE intervention is more effective but the costs are also more than in the wait-list group, incremental cost-effectiveness ratios will be computed, together with their CIs (using bootstrapping techniques to overcome the expected skewness of the cost data). Results will be plotted on a cost-effectiveness plane and presented as cost-effectiveness acceptability curves to show the probability of the intervention being cost-effective at a range of willingness-to-pay threshold levels. A sensitivity analysis will be conducted to take account of uncertainty and imprecision in the measurements, including multiple imputation models for missing values.

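### The bootstrapped confidence interval on the ICER, produced only when EASE looks better and dearer, can mix opposite conclusions; net benefit reported in every quadrant would not

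*Protocol article*

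**What the plan says.** The economic paragraphs of the Statistical analysis section link cost data to the primary and secondary outcomes, with internalising symptom scores singled out. The ICER is conditional on a comparison with the control arm: "In the event that dominance is not shown, that is, the EASE intervention is more effective but the costs are also more". Only if that condition is met does the plan say that "incremental cost-effectiveness ratios will be computed, together with their CIs (using bootstrapping techniques to overcome the expected skewness of the cost data"). The next sentence places the results on a cost-effectiveness plane and in acceptability curves over a range of willingness-to-pay thresholds. The paragraph ends: "A sensitivity analysis will be conducted to take account of uncertainty and imprecision in the measurements, including multiple imputation models for missing values".

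Cost-effectiveness is named in the study aim at the end of the Introduction. The abstract's aim and the Hypotheses section do not mention it.

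**The concern.** Two features of the stated rule cause difficulty.

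- **The condition covers only one kind of non-dominance.** Neither arm dominates when EASE is better and dearer, and equally when it is cheaper and less effective. The text names only the first, so the second has no stated numerical summary.
- **The condition acts on point estimates, but the interval is built from replicates.** A trial whose estimates lie in the better-and-dearer quadrant can have replicates in any of the four. A negative ratio arises both when EASE is cheaper and better and when it is dearer and worse. Sorting replicates by their ratio puts these opposite findings side by side at the bottom of the list. Close to zero effect, the ratio also jumps from very large positive to very large negative. The reason given for bootstrapping is skewed costs, which does not address either problem.

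At stake is the number most likely to be quoted from the economic evaluation. A reader may take a lower limit below zero as evidence that EASE could save money when the replicates behind it say dearer and worse.

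**Working it through.** The economic paragraphs state no numerical result to reproduce, so the check asks how often the stated interval misbehaves under the plan's own assumptions.

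**Inputs from the article**
- 564 adolescents "from 40 schools have been enrolled into the trial (14±3 average cluster size") (Abstract).
- ICC 0.05 and 40 schools (Sample size calculations: "with 80% power, 0.05 significance, an ICC of 0.05 and a two-sided hypothesis test with 40 school clusters").
- Attrition of 20% ("accounting for 20% attrition").
- Design effect size: "we assume an effect size of 0.4".

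**Assumptions not in the article**
- Smaller true effects of 0.2 and 0.1 SD, because costs are also linked to outcomes for which the trial was not sized.
- A true cost difference of 4 of its own standard errors, with 2 and 1 as less certain alternatives.
- Normal, independent cost and effect differences.

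**Step 1. Standard error of the effect**
- Analysed: 564 × 0.8 = 451, or 451.2/40 = 11.28 per school.
- Design effect: 1 + (11.28 − 1) × 0.05 = 1.514.
- SE in SD units: √(4 × 1.514/451.2) = 0.116.

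**Step 2. Share of replicates at or below zero effect when the estimate equals the true effect, Φ(−d/SE)**
- 0.4 SD: Φ(−3.45) = 0.03%.
- 0.2 SD: Φ(−1.73) = 4.2%.
- 0.1 SD: Φ(−0.86) = 19.4%.

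**Step 3. How often the interval goes negative.** Trials were simulated, and those with both point estimates positive were kept, as the rule requires. Replicates were drawn around each trial's estimates and the 2.5th percentile of cost/effect was taken. As a second check, a Fieller 95% set for the ratio is unbounded whenever the effect estimate is within 1.96 SE of zero.

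| True effect | Negative lower limit (cost difference 4 SE) | Fieller set unbounded, given better and dearer |
|---|---|---|
| 0.4 SD | about 9% | about 7% |
| 0.2 SD | about 59% | about 57% |
| 0.1 SD | about 82% | about 83% |

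Repeat simulations differ by only a point or two (9–10%, 58–59% and 82–84%).

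**Step 4. A less certain cost difference**
- Effect 0.4 SD, true cost difference 2 SE: about 53% of qualifying trials have a negative lower limit, mostly because of cheaper-and-better replicates.
- Effect estimate 0.4 SD, cost estimate 1 SE: about 16% of replicates are cheaper and better. The percentile interval runs from −2.6 to 10.0 around 2.5 (cost SEs per SD of effect).
- Effect estimate 0.2 SD, cost estimate 2 SE: about 4% of replicates are dearer and worse and about 2% are cheaper and better. The interval runs from −40 to 77 around 10, and its negative part contains both meanings.

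**The case against.** The strongest reply is that the sentence after the ICER rule already plans a cost-effectiveness plane and acceptability curves. Both carry the joint uncertainty in all four quadrants, and the curve is the probability of positive net benefit at each threshold. That stands: the evaluation as a whole is not left uninterpretable. It does not repair the ratio interval, which the plan still commits to reporting.

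Second, restricting the ICER to a quadrant where it expresses a trade-off is not in itself an error. That also stands. The faults are the omitted trade-off quadrant and an interval whose validity is judged from the point estimate alone. Nor does the condition show selective reporting: it is attached to the ICER and not clearly to the plane or curves.

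Third, the harmful mixing with dearer-and-worse replicates arises almost only when the effect is non-significant, which is about 6–7% of trials at 0.4 SD. This is correct, and it limits the size of the point for the PSC. It does not remove it for outcomes with smaller effects.

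A reader might also infer from the place given to imputation that the base case rests on participants with complete cost and outcome data, and so on a different set from the primary mixed model. The document does not support that. It never says complete cases, it leaves imputation detail to the statistical analysis plan, and linking costs to outcomes does not rule out a model-based effect estimate. Any bias figure would need further assumptions about who is lost and how they differ.

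**Conclusion.** The point holds in a limited form. The plan commits to a bootstrapped CI on a ratio, conditional on one quadrant, without providing for replicates that leave that quadrant. At the design effect of 0.4 SD the effect axis gives little trouble: 0.03% of replicates at or below zero when the estimate equals 0.4 SD, and about 9% of qualifying trials with a negative lower limit. At 0.2 SD or below, a negative limit is the usual result. If the cost difference is less certain than 4 SE, negative limits are frequent even at 0.4 SD, though mainly from replicates favourable to EASE.

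The effect-axis figures rest on the plan's ICC and attrition and the achieved enrolment. The negative-limit figures also need the assumed cost difference and independent normal increments, for which the article gives no data. This is worth correcting because a better summary is available from the same replicates, but it does not undermine the planned plane or acceptability curves.

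**What to change.** Reword the economic paragraphs, or settle the matter in the statistical analysis plan, which the article says will be finalised before unblinding:

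- Whatever the quadrant, report incremental cost, incremental effect and incremental net monetary benefit, each with a 95% CI, the last over the willingness-to-pay range. Use the same bootstrap replicates and present these beside the plane and acceptability curves.
- Give the ICER as a point estimate wherever it has a trade-off meaning, including cheaper and less effective. Give no ratio CI when replicates cross quadrants.
- Remove the wording that equates non-dominance with better and dearer.

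No new data are needed. The cost is rewording, a little more analysis, and a headline that may look less certain than a finite ICER interval would.

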### Qualitative process evaluation

Qualitative methods will be used to assess assumptions underlying the intervention strategy. In-depth interviews (IDIs) and focus group discussion (FGDs) will explore key programme implementation outcome variables and will cover intervention: acceptability, feasibility, appropriateness (including cultural appropriateness), fidelity, adoption and participants’ view about intervention’s perceived impact (both negative and positive) and ethics and safety concerns (Proctor, 2009). Following well-established procedures, qualitative interviews will be recorded, transcribed in Urdu and analysed in the original language (translation into English will only take place for the purpose of international reporting). IDIs and FGDs will be conducted at the preferred venue of the respondents, whether at home, at school or at any other place of convenience where privacy for IDIs/FDGs can be assured.

